**Fig. 1 Fig1:**
[figure not shown]
Flow of participants during the conduct of the trial

**Fig. 2 Fig2:**
[figure not shown]
Study content for the schedule of enrolment, interventions, and assessments. -t_2_: preoperative, -t_1_: 9^th^ postoperative day, t_0_: start of cardiac rehabilitation programme (3 weeks postoperative), t_1_: 4 weeks postoperative, t_2_: 5 weeks postoperative, t_3_: 9 weeks postoperative, t_4_: 12 weeks postoperative, t_5_: 12 months postoperative. SVC: slow vital capacity. VAS: visual analogue scale. MacNew QLQ: MacNew quality of life questionnaire

### Intervention

#### Cardiac rehabilitation programme

The cardiac rehabilitation programme is a multidisciplinary programme in line with the current guidelines. Components of the multidisciplinary programme include patient assessment, physical activity counselling, exercise training, diet/nutritional counselling, weight control management, lipid management, blood pressure monitoring, smoking cessation, and psychosocial management [22].

The outpatient exercise-based cardiac rehabilitation programme includes endurance training. No strength training exercises are executed. According to cardiac rehabilitation literature, all patients exercise under close supervision 3 days per week for a total duration of 3 months [28], and because this frequency is easily attainable for most patients. Exercise training intensity is determined by baseline Vo2peak assessment [29]. Patients exercise at a heart rate corresponding to 65% of baseline Vo2peak. Each exercise training session takes 45 min. Exercise time is apportioned as follows: 42% on the cycle ergometer, 33% on the treadmill and 25% on the arm-cranking device [30].

#### Osteopathic procedure

The protocol used for OT and osteopathic examination (OE) incorporates a number of osteopathic techniques and will be performed by five registered osteopaths with a minimum experience of 5 years. The protocol used is based on the work of Dickey [31] and supplemented with the findings of other authors [32–35]. The most common findings found in literature are:Decrease in costal mobility [8, 10, 11, 36]Decrease in pulmonary function [6, 8, 10]Decreased thoracic mobility [8, 10, 11, 31]Dysfunction of the abdominal diaphragm [31, 37–41]

The nomenclature, indications and contraindications for the OE and OT are based on the work of Nicholas and Nicholas [32], Chila [42], on the professional competence profile of an osteopath [43–45] and the benchmarks of the World Health Organisation [46].

The OE protocol is a set of standardised test for a first evaluation of the patient. The findings are noted on a predefined Microsoft excel-file by the Osteopath.Inspection: in standing, seated and supine: observe the patient in posterior, anterior and lateral view to develop the most complete understanding of the patients makeup before performing the remainder of the OE ([32] p. 3–14).Position test of the thoracic spine (seated) ([42] p.561)Intersegmental motion testing:thoracic seated ([32] p. 42–49)cervical supine ([32] p. 60–65)costal supine ([32] p. 52–59
Costal motion testing supine [32] (p.53–56)Evaluation of the abdominal diaphragm (seated and supine) ([42] p. 567)

The OT consists of a standardised treatment protocol (Table 1) and a supplementary treatment protocol of the dysfunctions found during the examination. In order to be reproducible, the different treatment possibilities are discussed and presented (Fig. 3). The OT will take 30–45 min. The examination room is air-conditioned and has a constant temperature of 21–22 °C. The OT will be performed at 4 weeks postoperative (t_1_), 5 weeks postoperative (t_2_), 9 weeks postoperative (t_3_) and at 12 weeks postoperative (t_4_). OT can be considered as safe, and major adverse events are very rare [47, 48]. In case adverse events should occur, they will be recorded and discussed in the final paper.

**Table 1 Tab1:** Standard treatment protocol OstinCaRe study

Osteopathic technique	Description	Rationale for use
Doming/stretching of the abdominal diaphragm [31–33]	Direct release of the respiratory diaphragm: the patient is supine and the osteopath stands on the homolateral side of the patient. The osteopath places the cubital side of the heterolateral hand under the anterior costal margin and the fingers of the homolateral hand under the posterior costal margin. During inspiration, the hands follow the expansion of the ribs and during expiration, the osteopath holds the expansion of the ribs. This is repeated 3–4 times on each side.	Improves motion of diaphragm Releases connective tissue tension within structures of the thorax
Myofascial release of the thorax [33]	One hand is placed posterior on one hemi thorax, the other hand anterior of the same hemi thorax (according to the anatomy of the ribs). Determine the direction of free movement with passive motion testing. Maintain either indirect or direct position until release. The osteopath stimulates the expression of the fasciae after the release.	Releases tissue restriction Promotes improved lymphatic and venous drainage Improves pulmonary function and lymphatic circulation
Suboccipital inhibition [31, 33, 34]	Fingertips are placed on occipital condyles. The osteopath applies an outward and cephalad traction to decompress the occipital joint	Improves parasympathetic function Releases restricted tissues around vagus nerves
Equilibration anterior-posterior [35]	One hand is placed under the sacrum and one hand on the sternum. The osteopath follows and synchronizes the expression of the primary respiration between sacrum and sternum. The same is done between the occiput and the sternum.	Improves lymphatic and venous circulation

**Fig. 3 Fig3:**
[figure not shown]
Supplementary osteopathic treatment protocol. Abbreviations: HVLA: high velocity low amplitude manipulation; MET: muscle energy technique

### Outcome measures

Primary outcome measure will be the mean difference in change from baseline in SVC at 12 weeks after surgery between the two groups.

Secondary outcome measures will include:Change from baseline in SVC at 52 weeksChange from baseline in MacNew QLQ at 12 and 52 weeks after surgeryChange in pain from baseline on Visual Analogue Scale (VAS) at 12 and 52 weeks after surgeryChange in thoracic stiffness from baseline on VAS at 12 and 52 weeks after surgeryChange from baseline in maximal aerobic capacity (VO2max) at 12 weeks after surgery

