## Methods/Design

### Aim of the study

The aim of this randomised controlled trial is to examine whether OT could lead to a better treatment of chronic thoracic pain, decreased pulmonary function and/or decreased thoracic mobility.

We hypothesized that OT reduces the decrease in SVC, reduces chronic thoracic pain, reduces thoracic stiffness and improves the quality of life in patients at 12 weeks and 52 weeks after CABG surgery.

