#### Spirometry

The Pocket-Spiro USB100 (Medical Electronic Construction & Logistic nv, Belgium) will be used for measuring pulmonary function. All patients are asked to perform a slow vital capacity (SVC) test, consisting of three measurements. For VC the best of the three measurements is used and for IVC the average of three measurements is used [49]. The instrument is calibrated prior to the test. When an OT is planned, SVC will be measured at least 2 days after OT, because the study wants to measure long-term effects (effects of the entire intervention), instead of any short-term effect (within the first hours after OT). SVC will be measured preoperative (-t_2_), 9^th^ postoperative day (-t_1_), 4 weeks after surgery (t_1_), 8 weeks after surgery (t_3_), 12 weeks after surgery (t_4_) and at 12 months after surgery (t_5_).

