#### MacNew quality of life questionnaire (QLQ) and Visual analogue scale (VAS)

The Flemish version of the MacNew QLQ and the VAS for pain and thoracic stiffness are delivered to the patients by a blinded person of the cardiac rehabilitation centre at enrolment (t_0_), 12 weeks after surgery (t_4_) and at 12 months after surgery (t_5_). The Flemish version of the MacNew QLQ demonstrates good psychometric properties and is recommended as a specific instrument for assessing and evaluate health-related quality of life in Flemish-speaking patients [52].

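### The primary outcome is a change from a baseline SVC visit that is never named, and one candidate, week 4, follows the first osteopathic treatment if the 2-day rule is read literally

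*Protocol article*

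**What the plan says.** The Outcome measures section defines the primary outcome as the mean difference in "change from baseline in SVC at 12 weeks after surgery between the two groups". The Abstract says the same. The 52-week SVC outcome is also a change from baseline. Neither place names the baseline visit.

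The Spirometry section gives the schedule: "SVC will be measured preoperative (-t_2_), 9^th^ postoperative day (-t_1_), 4 weeks after surgery (t_1"), then week 8, week 12 and 12 months. Three SVC measurements could therefore serve as baseline. The same section sets a timing rule: "When an OT is planned, SVC will be measured at least 2 days after OT". Its stated purpose is to capture long-term effects, not those of the first hours after a treatment.

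The Osteopathic procedure section places the first treatment at the same time point as the third SVC: "The OT will be performed at 4 weeks postoperative (t_1").

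The questionnaires are given "at enrolment (t_0_), 12 weeks after surgery (t_4_) and at 12 months after surgery (t_5"). The Fig. 2 legend puts t0 at 3 weeks after surgery. No SVC is scheduled there.

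The Aim of the study says: "We hypothesized that OT reduces the decrease in SVC". The Sample size section rests on a 12% decrease in IVC at 12 weeks after surgery and expects treatment to recover about that amount.

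Under Statistical analysis, normally distributed data go to repeated-measures ANOVA. Otherwise absolute changes are compared by Mann-Whitney tests. Covariates enter only when baseline differences are found.

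**The concern.** A change score is defined only once both of its visits are fixed. Here the end visit is fixed and the starting visit is not. The article's use of the word elsewhere does not settle it, because baseline has to mean different visits for different outcomes. For the questionnaires it is t0, where SVC is not measured. For maximal aerobic capacity it can only be t1, the first exercise test. So t1 already serves as a baseline visit in this plan.

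Two things are at stake. If t1 SVC were the baseline and had been taken after the first treatment in group B, part of any treatment effect would be subtracted from that group only. Separately, an unnamed baseline leaves room to choose between visits after the data are seen, and different visits give different p-values.

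**Working it through.** **Step 1. Which visits qualify.** Candidates from Spirometry, set against the first treatment at week 4 (Osteopathic procedure):

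| SVC visit | Relation to first treatment | Textual support as baseline |
|---|---|---|
| Preoperative (-t2) | before | Aim and Sample size speak of a decrease after surgery; Background gives a fall of 30–60% in the first week and a remaining 12% reduction at up to 1 year |
| Day 9 (-t1) | before | none specific |
| Week 4 (t1) | same time point; at least 2 days after it in group B if the rule is read literally | first exercise-test visit, hence the baseline for aerobic capacity |

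**Step 2. The two pre-treatment visits.** Let B be any SVC measured before treatment and Y the week-12 SVC. Under randomisation E(B) is equal in both groups, so the expected between-group difference in Y − B equals the expected difference in Y. This holds for both -t2 and -t1. They estimate the same treatment effect and differ in precision and in the realised estimate.

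**Step 3. The week-4 visit.** If a share g of the 12-week effect d is already present in group B at t1, the expected difference in change is d(1 − g).

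Inputs: d = 0.50, alpha 0.05 two-sided, power 0.80 and 128 per group, from Sample size and Statistical analysis. The values of g are assumed; the article gives none.

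The plan's own figure first: d = 0.50 with 80% power needs 64 per group by the two-sample t-test, so the stated 128 equals the total for both groups (2 × 64). That is a separate matter. The calculation below uses 128 per group because it is the plan's stated size.

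Power is from the noncentral t distribution with 254 degrees of freedom and noncentrality d(1 − g) × √(128/2) = 8d(1 − g):

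| g (assumed) | d(1 − g) | noncentrality | power |
|---|---|---|---|
| 0 | 0.50 | 4.0 | 97.9% |
| 10% | 0.45 | 3.6 | 94.8% |
| 25% | 0.375 | 3.0 | 84.8% |

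**Step 4. Choosing between the two unbiased baselines.** With equal variances and equal correlation rho between visits, Y − B1 and Y − B2 have variance 2σ²(1 − rho) and covariance σ²(1 − rho), so they correlate 0.5 whatever rho is. For two test statistics correlated 0.5, P(max |Z| > 1.96) = 9.1%, against a nominal 5%.

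**Step 5. What prespecified adjustment gains.** With equal variances at both visits, the variance of the treatment estimate is proportional to:
- change score: 2σ²(1 − rho)
- ANCOVA on the baseline value: σ²(1 − rho²)
- ratio: (1 − rho²) / [2(1 − rho)] = (1 + rho)/2

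At rho = 0.5 the ratio is 0.75 (25% lower); at rho = 0.7 it is 0.85 (15% lower). Both correlations are assumed.

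**The case against.** The strongest reply is that the article's reasoning mostly converges on the preoperative value. Background, Aim and Sample size all describe a loss caused by surgery, and the gain expected in Sample size is the reversal of that loss. This stands: preoperative is the most natural reading. It is still an inference, because no section states it.

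Second, the 2-day rule can be read as a washout that only forbids SVC shortly after a treatment. A week-4 SVC could then precede the first treatment. The stated purpose of the rule allows this, but the text does not say so. The post-treatment status of t1 therefore depends on the literal reading.

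Third, in a repeated-measures ANOVA that includes the listed visits, the group-by-time interaction does not depend on which visit is called baseline. That is correct. The ambiguity bites on the outcome as defined, which is a change, and on the Mann-Whitney route, which compares absolute changes.

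Fourth, the article is condensed and a fuller document might name the visit. If the missing name were all, this would be close to omitted detail. The week-4 overlap, however, lies between two statements printed here, and the data-driven covariate rule is also printed.

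A reader might infer more than the article supports:
- **That the baselines measure different treatment effects (residual loss versus recovery).** The meaning of the within-group change differs, but by Step 2 the preoperative and day-9 visits share one expected between-group difference.
- **That type I error is about 12.5%.** That requires picking the best of all three visits, including one that may follow treatment. Nothing indicates such a choice, and a statistician blinded to allocation makes it less likely.
- **That power falls to 71–56%.** Those figures apply at 64 per group, which is not the plan's stated size.

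**Conclusion.** The concern holds in limited form. The baseline visit of the primary outcome is not fixed. The preoperative value is the likely intention, but t1 is not excluded.

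Only a t1 baseline would bias the result, and only if the 2-day rule is applied literally. The bias would be toward no difference. With 10–25% of the effect present by then (assumed), power at 128 per group would fall from about 98% to 95–85%, still above the planned 80%.

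Between the two pre-treatment visits there is no bias. The exposure is a type I error of about 9% if the better result of the two were selected. That figure assumes equal variances and equal correlation between visits, and it is a worst case, not a prediction.

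The practical gain from settling the matter is a uniquely defined primary variable and, with ANCOVA, a lower variance of the treatment estimate: 25% lower than a change-score analysis at rho 0.5 and 15% lower at rho 0.7.

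**What to change.** 1. In Outcome measures, name the preoperative SVC (-t2) as baseline for both the 12-week and the 52-week SVC outcomes, and state that the t1 SVC is not used as baseline.
2. Reconcile Osteopathic procedure with Spirometry on the order of SVC and treatment at week 4, and state how the 2-day rule applies at that visit.
3. In Statistical analysis, make the primary analysis an ANCOVA of week-12 SVC with preoperative SVC as a prespecified covariate, in place of adding covariates only when baseline differences appear. Day-9 SVC may be added as a second pre-treatment covariate; this is optional.

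The cost is a few sentences. The preoperative SVC is already scheduled, so no extra measurement or patient is needed.

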#### Spirometry

The Pocket-Spiro USB100 (Medical Electronic Construction & Logistic nv, Belgium) will be used for measuring pulmonary function. All patients are asked to perform a slow vital capacity (SVC) test, consisting of three measurements. For VC the best of the three measurements is used and for IVC the average of three measurements is used [49]. The instrument is calibrated prior to the test. When an OT is planned, SVC will be measured at least 2 days after OT, because the study wants to measure long-term effects (effects of the entire intervention), instead of any short-term effect (within the first hours after OT). SVC will be measured preoperative (-t_2_), 9^th^ postoperative day (-t_1_), 4 weeks after surgery (t_1_), 8 weeks after surgery (t_3_), 12 weeks after surgery (t_4_) and at 12 months after surgery (t_5_).

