### Design

OstinCaRe stands for Osteopathy in Cardiac Rehabilitation. The OstinCare-study is designed as a randomised controlled trial with two parallel groups. Group A will receive a standard exercise-based cardiac rehabilitation programme and group B will receive a standard exercise-based cardiac rehabilitation programme with four additional osteopathic treatments. The study will be performed at the Jessa Hospital Hasselt, Belgium.

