### Randomisation and masking

Patients will be randomly assigned in a 1:1 ratio to either group A or group B (Fig. 1). A blocked allocation schedule will be used. Randomisation will be performed by means of opaque, sealed envelopes. A physical therapist of the cardiac rehabilitation centre will perform and store the randomisation. The personnel of the cardiac rehabilitation centre performing the outcome measurements in this study are unaware of patient’s allocation. Osteopathic treatments will not be performed in the presence of the personnel of the cardiac rehabilitation centre. The treatments will be performed in another location to assure that the personnel of the cardiac rehabilitation centre remains blinded to patient’s allocation. Only the treating osteopaths will be aware of the patient’s allocation. The enrolment and procedures are visualised in Fig. 2 according to the Standard Protocol Items: Recommendations for Interventional Trials (SPIRIT) guidelines [26, 27].

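### The spirometry timing rule hangs on osteopathic treatment, which only group B receives, so equal timing and concealed allocation are not assured at the week-12 primary measurement

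*Protocol article*

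**What the plan says.** - **Primary outcome** (Outcome measures): "Primary outcome measure will be the mean difference in change from baseline in SVC at 12 weeks after surgery between the two groups".
- **Timing rule** (Spirometry): "When an OT is planned, SVC will be measured at least 2 days after OT". The reason follows at once: "because the study wants to measure long-term effects (effects of the entire intervention), instead of any short-term effect (within the first hours after OT". The rule gives a minimum gap, no maximum, and nothing that applies to a patient without OT.
- **SVC schedule** (Spirometry): the visits are set by time since surgery, and the last two are "12 weeks after surgery (t_4_) and at 12 months after surgery (t_5").
- **Who has OT** (Design): "group B will receive a standard exercise-based cardiac rehabilitation programme with four additional osteopathic treatments". Group A has none.
- **OT schedule** (Osteopathic procedure): weeks 4 and 5, then "9 weeks postoperative (t_3_) and at 12 weeks postoperative (t_4").
- **Masking** (Randomisation and masking): "The personnel of the cardiac rehabilitation centre performing the outcome measurements in this study are unaware" of allocation. Knowledge of it is restricted to the treating osteopaths, and OT is given at a separate location to keep the rehabilitation staff blinded.

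**The concern.** A measurement that defines the primary outcome should be scheduled the same way in both groups. Here a stated rule makes its date depend on an event that occurs in one group only. Two things could go wrong.

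1. **Timing.** If group B is tested some days later than group A while lung volume is still recovering, part of any difference reflects elapsed time, not treatment.
2. **Blinding.** Someone has to know whether and when an OT took place in order to apply the rule. If that person books or performs the spirometry, the date itself discloses the group. SVC needs patient effort, and the plan takes the best of three attempts for VC. The Abstract claims blinding for rehabilitation staff and outcome assessors, not for patients, so assessor blinding is the main protection of this outcome.

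**Working it through.** **Step 1: does the rule reach the primary measurement, and in which group?**

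| Visit | OT (group B only) | SVC (both groups) | Same nominal time? |
|---|---|---|---|
| t1 | week 4 | week 4 | yes |
| t3 | week 8 (Abstract) or week 9 (Fig. 2 legend, Osteopathic procedure) | week 8 (Spirometry) | depends on which section is followed |
| t4, primary | week 12 | week 12 | yes |

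The condition can arise only in group B, and it arises at the primary time point. Week 4 overlaps too, but the Outcome measures section names no week-4 or week-8 SVC endpoint.

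**Step 2: who can apply the rule?** The document assigns the booking of SVC and OT to nobody. There are two possibilities.

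- The osteopaths place the OT ahead of a known SVC date. No information passes to the assessors, and the masking statement holds.
- The spirometry staff place the SVC after a known OT date. They then learn who had OT, and the masking statement fails.

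The sentence in the Spirometry section takes OT as the anchor and SVC as the event being timed. Its wording is therefore closer to the second possibility, but it does not exclude the first.

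**Step 3: how large could the timing bias be at week 12?** The plan gives no figure for this, so there is none to reproduce.

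Inputs: a VC loss of 30 to 60% in the first week (Background), taken as day 7; an IVC loss of 12% at 12 weeks (Sample size), day 84; a planned gain of 12% (Sample size), read as 12 points. VC and IVC are treated as interchangeable, which is an assumption. So is the length of the delay: 2 days is the stated minimum gap, and 7 days illustrates the missing upper limit.

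Linear slope = (early loss − 12) / (84 − 7). Bias = slope × delay.

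| Early loss | Slope, points/day | 2-day delay | 7-day delay |
|---|---|---|---|
| 30% | 18/77 = 0.23 | 0.5 points (4% of 12) | 1.6 points (14%) |
| 45% | 33/77 = 0.43 | 0.9 points (7%) | 3.0 points (25%) |
| 60% | 48/77 = 0.62 | 1.2 points (10%) | 4.4 points (36%) |

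A straight line spreads fast early recovery evenly up to week 12. If recovery slows with time, these are upper figures for t4.

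**Step 4: check against the later figure.** The Background section puts the VC loss at 12% even up to 1 year, the same as the 12-week loss used for planning. From week 12 to 1 year the slope is then (12 − 12) / (365 − 84) = 0 points per day, and a delay of a few days adds almost nothing.

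**The case against.** The rule fixes a gap between two events and does not say which of them moves. The same section sets SVC by time since surgery for everyone. Both statements are met if the fourth OT comes early in week 12 and SVC follows later that week, on the same day as in group A. OT is given elsewhere, and only the osteopaths are said to know allocation, so they could arrange this without telling the assessors anything. All patients train at the centre three days a week, so a test one session later need not stand out. Visit windows and booking duties are also details that an article may leave to the full protocol.

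Much of this stands. A reader might infer that group B is systematically measured later, that spirometry staff must know about OT, or that late measurement favours OT at week 12. The document supports none of these: the first two depend on how a site applies the rule, and the third conflicts with the equal 12% losses in Step 4. Nor can one say that every intermediate visit is shifted, because with OT at week 9 and SVC at week 8 the two do not coincide.

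The objection does not remove the core. The point concerns a rule that the article states, not a detail it leaves out. That rule is conditional on OT and acts at t4, and nothing in the text directs a site to the harmless way of meeting it.

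**Conclusion.** The point holds in a limited form. As worded, the rule can make group B's primary SVC later than group A's, and it can disclose allocation if those who book or perform spirometry apply it. It sits badly with the statement that only the treating osteopaths know allocation.

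The direct timing bias at week 12 is probably minor: at most about 0.5 to 1.2 points for 2 days, assuming that recovery is no faster at week 12 than its average since week 1, and near zero on the document's own later figure. A delay of a week, which the rule does not forbid, has an upper range of 1.6 to 4.4 points under the same assumption. The threat to concealment matters more. It does not depend on the recovery slope, and the document gives nothing from which to quantify it. Neither unequal timing nor broken blinding is shown to have happened.

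**What to change.** 1. Set the date of each SVC by days since surgery, with one identical window in both groups.
2. Reword the Spirometry rule so that the SVC date no longer depends on OT. Make the unblinded osteopaths, not the spirometry staff, responsible for the plan's own minimum gap, by completing the OT before the fixed SVC date. The word before matters: asking only for distance from the SVC date would let the fourth OT fall after the primary measurement, against the stated aim of capturing the whole intervention.
3. Report days from surgery to SVC by group, so that readers can see whether timing was comparable.
4. Reconcile the t3 times for OT and SVC (week 8 or week 9) across the Abstract, the Fig. 2 legend, Osteopathic procedure and Spirometry.

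This is a scheduling amendment and needs no extra visit, procedure or staff. It leaves less freedom in booking OT. Recruitment began in January 2010, so the change does not affect patients already measured; for them, item 3 is the available check where both dates are on file.
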